**Conclusions:**

An estimated 8-10% of patients will develop AL following surgery, and they will be compared to non-leakage patients. The objectives of this study are twofold. The primary aim is to establish and validate a diagnostic algorithm for the pre-operative prediction of the risk of AL development using a combination of inflammatory, immune-related, and genetic parameters. Previously established risk factors and novel parameters will be incorporated into this algorithm, which will aid in the recognition of patients who are at risk for AL. Based on these results, recommendations can be made regarding the construction of an anastomosis or deviating stoma, and possible preventive strategies. Furthermore, we aim to develop a new algorithm for the post-operative diagnosis of AL at an earlier stage, which will positively reflect on short-term survival rates.

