## Introduction

Surgery remains the predominant curative treatment for patients with colorectal cancer (CRC), but can lead to severe post-operative complications, of which anastomotic leakage (AL) is the most feared. AL occurs in 8-15% of patients undergoing colorectal surgery and is associated with high morbidity and short-term mortality rates of up to 39% [1-4]. AL often requires one or more re-interventions, leading to a significant increase in length of hospital stay and subsequently to high health care costs [3]. Some authors even suggest that AL is associated with an impaired oncological prognosis [5-8]. Both decreased disease-specific survival (odds ratio [OR] 1.75) [9,10] and an increased local recurrence rate of CRC (OR 2.9) [10] have been reported.

In the past decades, important risk factors for AL such as male gender [4], neo-adjuvant chemotherapy [11], tumor size [12], malnutrition [13], smoking [14], steroid treatment [1,15], and the use of non-steroidal anti-inflammatory drugs (NSAIDs) [16] have been identified. Despite the determination of these risk factors for AL, surgeons’ prediction of the risk to develop AL for the individual patient remains inaccurate [17]. Despite decades of extensive research on preventive methods, the introduction of innovative surgical techniques, and fast-track protocols, incidence rates of AL have remained stable [18].

A recently conducted study in one of the participating centers, that can be considered a pilot study, suggests that pre-operative levels of a certain plasma marker (intestinal fatty acid binding protein, I-FABP) can predict the development of AL in patients undergoing CRC surgery. I-FABP is present in mature enterocytes of the small and large intestine, and is released upon intestinal damage [19]. It is hypothesized that increased plasma levels of I-FABP are the result of an underlying clinical condition of the gastrointestinal tract, predisposing the patient to AL [20].

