**Statistical Analyses**

The sample size is calculated with a power analysis and is aimed at our main study outcome, AL. From literature, we know that approximately 10% of all colorectal patients receiving an anastomosis will develop AL [14,37]. The aim of the study is to detect significant and clinically relevant differences between the AL group and the non-AL group. Therefore, we used data from a previous study undertaken by our group to determine sample size [20]. We chose our least significant finding, to avoid the study being underpowered. Based on an effect size of 0.41 (calculated with mean calprotectin levels and SD on day 1), with a power of 0.80 and a 95% confidence interval, the total sample size will be 560, of whom an estimated 51 patients will develop AL. Assuming a 5% dropout rate, the total number of patients that needs to be included in this study is 588.

After data collection, normality will be tested by the D’Agostino-Pearson test. Student’s t-tests will be used for between-group comparisons for continuous data. Dichotomous variables will be compared using Pearson’s chi-squared test. All data will be presented as mean and standard error of the mean. The area under the curve of receiver operating characteristic (ROC) curves will be used to calculate the diagnostic ability of the studied markers predicting AL. The area under the ROC curve is a summary measure of accuracy, lying in the range from 0.5 to 1, with 1 indicating perfect discrimination and 0.5 indicating no discrimination capacity. To determine the most ideal combination of markers, logistic regression analyses will be performed.

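### The stated analysis is not tied to the established risk factors that the algorithm is meant to include, so single-marker or total AUCs will not show what the novel parameters add

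*Protocol article*

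**What the plan says.** The Protocol article describes the content of the pre-operative algorithm in the Conclusions of its Abstract: "Previously established risk factors and novel parameters will be incorporated into this algorithm". The Introduction names known factors, beginning with "important risk factors for AL such as male gender" and going on to neo-adjuvant chemotherapy, tumor size, malnutrition, smoking, steroids and NSAIDs. It adds that surgeons still predict individual risk poorly despite knowing them.

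The Statistical Analyses section lists t-tests and chi-squared tests between the leakage and non-leakage groups and ROC AUCs for the studied markers. It closes with: "To determine the most ideal combination of markers, logistic regression analyses will be performed". It names no base model of established factors, does not say that these factors are kept in the regression, and states no comparison of performance with and without the novel parameters.

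The sample size has the same marker-alone form. Its key input is one marker's group difference: "effect size of 0.41 (calculated with mean calprotectin levels and SD on day 1". Power is set at 80% and the confidence level at 95%. The outcome of the calculation is stated as follows: "the total sample size will be 560, of whom an estimated 51 patients will develop AL".

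**The concern.** The Abstract describes a model of old and new predictors together. The analysis section describes markers one at a time and then markers combined. The two do not quite meet.

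The gap matters because the novel measurements (buccal swab, breath, stool and blood) are justified in the Introduction by the shortcomings of what surgeons already know. A marker can differ between groups and have a fair AUC of its own simply because it tracks a known risk factor. If the established factors are in the final model, its total AUC mixes their contribution with that of the novel parameters. On either reading, the accuracy measures named in the plan leave open whether the additional sampling improves the risk estimate. The Study Objectives section intends that estimate to inform decisions about anastomoses and deviating ostomies.

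**Working it through.** **1. Reproduce the plan's own figure.**

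Inputs from Statistical Analyses: d = 0.41, power 0.80, and a 95% confidence level read as two-sided alpha 0.05 (sidedness is not stated). With 51 leaks in 560 patients, the ratio of non-leak to leak is 509/51, about 10.

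Leak group size = (1 + 1/k)(z₀.₉₇₅ + z₀.₈₀)²/d² = 1.1 × (1.960 + 0.842)²/0.41² = 1.1 × 7.85/0.1681 = 51.4. Rounded up to 52, the total is 52 × 11 = 572, within 3% of 560. Conversely, 51 leaks and 509 non-leaks give power 0.797 (0.796 by the t-test). The inclusion target also follows: 560 × 1.05 = 588.

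The study is therefore sized for an unadjusted difference in one marker.

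**2. The marker alone.**

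Under a binormal model, AUC = Φ(d/√2) = Φ(0.41/1.414) = 0.614.

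**3. The marker added to established factors.**

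Assumptions that are not in the documents: the established factors form a score with AUC 0.65 or 0.70, and the within-group correlation ρ between marker and score is 0, 0.3 or 0.5. The score's effect is d_S = √2 × Φ⁻¹(AUC), which is 0.545 or 0.742.

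Combined d² = (d_S² + d_M² − 2ρ d_S d_M)/(1 − ρ²), with d_M = 0.41.

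Worked example, base 0.70 and ρ = 0.3: (0.550 + 0.168 − 0.182)/0.91 = 0.589, so d = 0.767 and AUC = Φ(0.767/1.414) = 0.706.

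| Base AUC | ρ | AUC with marker | Gain | Power of nested test | Power of marker's own t-test |
|---|---|---|---|---|---|
| 0.65 | 0 | 0.685 | 0.035 | 0.79 | 0.79 |
| 0.65 | 0.3 | 0.665 | 0.015 | 0.43 | 0.80 |
| 0.65 | 0.5 | 0.656 | 0.006 | 0.20 | 0.78 |
| 0.70 | 0 | 0.725 | 0.025 | 0.78 | 0.78 |
| 0.70 | 0.3 | 0.706 | 0.006 | 0.26 | 0.80 |
| 0.70 | 0.5 | 0.700 | 0.000 | 0.06 | 0.80 |

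The power columns come from simulation: 51 leaks, 509 non-leaks, 600 runs per row, with a likelihood-ratio test of nested logistic models. The marker's own test looks the same in every row, while what it adds does not.

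The near-zero gain in the last row arises because ρ is close to d_M/d_S = 0.41/0.742 = 0.55, the value at which the marker adds nothing. A negative correlation would give a larger gain than any shown.

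**4. Room for predictors.**

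With 51 events, 5 candidate predictors leave 51/5 = 10.2 events each, 10 leave 5.1, and 20 leave 2.55.

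**The case against.** A reader might infer that the plan cannot show added value at all, or that a marker which merely mirrors a known factor would pass every stated step. The documents do not support either. If the Abstract is read together with the analysis section, the established factors are in the logistic regression, and a redundant marker would get an adjusted coefficient near zero. In the last row above its weight is proportional to 0.41 − 0.5 × 0.74 = 0.04, and a nested test would flag it in only about 6% of studies. Logistic regression is also the right tool for the comparison, and nothing in the plan rules the comparison out.

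Four further points stand.

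- Superiority over established factors is never a formal hypothesis. It is only implied by the study's rationale.
- This is a condensed article, and a full protocol or analysis plan may specify the models. The absence of a nested test is therefore not in itself an error. The point rests on the mismatch between two statements that the article does make.
- The effect of 0.41 comes from day-1 calprotectin, apparently the post-operative day-1 sample. It is not a pre-operative marker effect.
- The article promises only several baseline characteristics, so not every factor in the Introduction is shown to be recorded. Some cannot cleanly serve as base factors here: NSAIDs are withheld perioperatively, and nutritional scores are themselves study parameters.

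What does not fall is the central point. The regression is described as a search among markers, and neither single-marker AUCs nor a total AUC isolates the contribution of the novel parameters.

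**Conclusion.** The concern holds in a limited form. The Abstract commits the algorithm to established factors plus novel parameters, the Statistical Analyses section does not tie its regression to the established factors, and the accuracy measures it names do not show what the novel parameters add. Under the assumed base AUCs and correlations, a marker that meets the planning effect adds between about 0.035 and 0 to the AUC. This range is illustrative: it rests on binormality, on base AUCs and correlations that the documents do not give, and on a planning effect from a day-1 marker. The weakness lies in the stated analysis and not in the data, and it can be mended without redesign.

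**What to change.** State in Statistical Analyses that the logistic regression for the pre-operative tool starts from a small, prespecified base model of the established pre-operative factors that the study records. A limited, prespecified set of novel parameters is then added. Say on which side the nutritional measures fall. Report the likelihood-ratio test for the addition and the optimism-corrected change in AUC with its 95% interval, and base any claim about the novel parameters on that comparison and not on single-marker AUCs. Net benefit over the base model is optional.

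The change needs no new patients or samples. It costs a little more analysis and a real limit on the number of candidate predictors, given about 51 expected events. The reported benefit of the markers may also turn out smaller.

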Cumulative evidence in the literature suggests that perioperative pain treatment with NSAIDs, commonly prescribed analgesics that inhibit cyclo-oxygenase 2 (COX-2) expression, increase the risk of AL [16,21,22]. COX-2 knockout mice have an increased risk of developing AL, and this risk can be reduced by the administration of prostaglandin E2, a product of COX-2 [23]. Another study conducted by our research group has demonstrated that decreased COX-2 expression, due to a polymorphism in the COX-2 gene, leads to an increased risk of the development of AL [23]. Furthermore, it has been shown that patients with different genotypes of mannose-binding lectin (MBL), an important complement factor of the immune system, respond differently to intestinal damage [24].

In the pilot study mentioned previously, it was shown that a combination of C-reactive protein (CRP) and calprotectin levels in plasma provides high diagnostic accuracy for AL during the post-operative period. Finally, we have shown that functional compromise (characterized by malnutrition, frailty, and sarcopenia) is associated with post-operative morbidity and mortality [25]. Malnutrition, as indicated by high Short Nutritional Assessment Questionnaire (SNAQ) scores, and sarcopenia were predictive for, or showed a trend towards, prediction of AL.

Based on previous literature and both our experimental and clinical data, we hypothesize that the occurrence of AL is partly due to patient-derived factors such as a compromised immune response, sarcopenia, genetic predisposition, and an aberrant intestinal microbiome composition, and that the post-operative course can be further influenced by surgical stress, ischemia, and a derailed systemic response. Our hypothesis is that, based on these parameters, individual risks for the development of AL can be assessed pre-operatively.

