Upon hospital admission, a buccal swab will be performed in order to collect DNA to screen for MBL and COX-2 polymorphisms. In addition, composition of volatile organic compounds (VOCs) in exhaled air will be measured both pre- and post-operatively. Various metabolic processes produce markers that are released into the circulation and, upon passage through the pulmonary system, can be identified as volatile products in exhaled air. The occurrence of (chronic) inflammation and/or oxidative stress can result in the excretion of volatile compounds that generate unique VOC patterns [32]. Furthermore, several baseline characteristics will be acquired prior to surgery, and stool will be collected on three occasions (pre-operatively, post-operatively and at the outpatient department during a control visit) in which the intestinal microbiome can be identified. It has been suggested that the microbiota play an important role in the pathogenesis of AL [33] and that the composition of the intestinal flora can be altered by surgical stress [34]. Plasma will be collected prior to surgery and on post-operative days 1, 3, and 5, in order to determine the concentration of markers for enterocyte damage (eg, I-FABP, citrullin, and calprotectin), transmural ischemia (eg, smooth muscle protein 22), and general inflammation markers (eg, CRP and leukocyte count).

In addition, SNAQ and Malnutrition Universal Screening Tool scores are obtained to assess the nutritional status of the patient, and CT-images are analyzed for total skeletal muscle cross-sectional area in order to distinguish sarcopenic patients from those in good nutritional health [25]. Generalized atherosclerosis will be assessed using abdominal CT-scans, as this is a proposed risk factor for AL [35,36]. Finally, a tissue sample will be obtained from the resected specimen, on which conventional and immunohistochemical staining will be performed.

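### Post-operative marker combinations are handled only by a data-driven search, so the pilot's CRP plus calprotectin pair is never named for a test independent of that search

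*Protocol article*

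**What the plan says.** The Introduction describes a recent study in one of the participating centers "that can be considered a pilot study, suggests that pre-operative levels of a certain plasma marker" (I-FABP) can foretell leakage. From the same pilot it reports that "a combination of C-reactive protein (CRP) and calprotectin levels in plasma provides high diagnostic accuracy for AL during the post-operative period". It gives no coefficients, cut-off, AUC or sampling day for that pair.

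Under Study Outline, plasma is taken before surgery and on days 1, 3 and 5 for "markers for enterocyte damage (eg, I-FABP, citrullin, and calprotectin"), smooth muscle protein 22, CRP and leukocyte count. Both members of the pilot pair are therefore measured again.

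Statistical Analyses takes an effect size from the group's previous study: "Based on an effect size of 0.41 (calculated with mean calprotectin levels and SD on day 1"). It then plans t-tests, chi-squared tests and ROC areas for the studied markers. Its only sentence on combinations is: "To determine the most ideal combination of markers, logistic regression analyses will be performed".

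**The concern.** A combination found in earlier patients and measured again in new ones can be assessed without selection. The plan does not set this up. CRP plus calprotectin is pooled with every other marker and day, and the regression picks the winner.

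Two things follow. First, the replication question, whether the pilot pair works in new patients, gets no pre-specified answer. If the pair disappoints, another combination can take its place in the report. Second, a winner chosen and assessed in the same patients has an AUC that is too high on average. A reader who wants to know whether to trust post-operative CRP plus calprotectin would get a less useful answer than the same data could give.

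**Working it through.** **1. The plan's own figure.** Inputs from Statistical Analyses: d = 0.41; "with a power of 0.80 and a 95% confidence interval" (read as two-sided 5%); "approximately 10% of all colorectal patients receiving an anastomosis will develop AL"; "the total sample size will be 560, of whom an estimated 51 patients will develop AL". The last figure is close to one leak per ten non-leaks.

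Leaks needed = (1.960 + 0.842)² × (1 + 1/10) / 0.41² = 7.849 × 1.1 / 0.1681 = 51.4. Rounded to 51, the total is 51 × 11 = 561, against 560 stated. Power with 51 v 509 is 0.797. The figure is reproduced, so 51 leaks and 509 non-leaks are used below.

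**2. Precision for a rule fixed in advance.** Hanley-McNeil: SE² = [A(1−A) + (n1−1)(Q1−A²) + (n0−1)(Q2−A²)] / (n1·n0), where Q1 = A/(2−A) and Q2 = 2A²/(1+A). The documents give no AUC, so A is assumed.

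At A = 0.80: Q1 = 0.6667 and Q2 = 0.7111. The numerator is 0.16 + 50 × 0.0267 + 508 × 0.0711 = 37.62, and the denominator is 51 × 509 = 25,959. SE = 0.0381, and the half-width is 1.96 × 0.0381 = 0.075. The same formula gives 0.083 at A = 0.70 and 0.057 at A = 0.90.

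**3. Optimism of a searched pair.** Six plasma markers are named. On three post-operative days they give 18 marker-days and 18 × 17 / 2 = 153 pairs. Simulation: 51 v 509 patients, normal markers with equal within-group correlation, 300 runs per row. In each run the pair with the largest in-sample discriminant distance is chosen. The effects and correlations are assumptions, and the pilot pair is assumed to be truly the strongest.

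| Correlation | d, pilot pair | d, other 16 | Searched pair: apparent / true AUC | Gap | Named pair refitted: gap | Named pair, fixed weights: mean / true AUC |
|---|---|---|---|---|---|---|
| 0.3 | 0.41 | 0 | 0.672 / 0.610 | 0.062 | 0.012 | 0.640 / 0.640 |
| 0.3 | 0.41 | 0.2 | 0.660 / 0.601 | 0.059 | 0.010 | 0.638 / 0.640 |
| 0.5 | 0.41 | 0.2 | 0.659 / 0.592 | 0.067 | 0.017 | 0.635 / 0.631 |
| 0.5 | 0.6 | 0.3 | 0.699 / 0.660 | 0.040 | 0.009 | 0.688 / 0.688 |
| 0.3 | 0.6 | 0.2 | 0.709 / 0.682 | 0.027 | 0.008 | 0.702 / 0.701 |

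**4. A wider model.** If all candidates are fitted together (two true markers with d = 0.41, the rest noise, uncorrelated, 200 runs), apparent against true AUC is 0.68 v 0.63 with 5 candidates and 0.76 v 0.59 with 30. These gaps are 0.05 and 0.17. A fixed equal-weight score of the two true markers averages about 0.66 against a true 0.659.

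Most of the bias comes from selection. Naming the pair removes most of it, and freezing the weights removes the remaining 0.01 or so.

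**The case against.** The strongest reply is that a search suits the study's purpose, which is a multi-parameter tool. Nothing excludes scoring the pilot pair as well, and a condensed article may leave such an analysis to a fuller document. This stands to a degree: the plan does not prohibit the test. But the article does say how combinations will be handled, and the method it states is the search.

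Four stronger readings are tempting, and the documents do not support them.

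- *That I-FABP also goes untested.* ROC areas are planned for the studied markers. A single marker needs no coefficients for its AUC, so pre-operative I-FABP gets a selection-free result. CRP and calprotectin taken singly are covered in the same way, so a failure could not be wholly hidden. The gap is the pair.
- *That the study gives up its only unbiased validation.* Bootstrap or cross-validation correction, or leaving out one of the three centers, can give nearly unbiased estimates for a new model. They answer a different question from whether the pilot pair replicates.
- *That this would be fully external validation, or would serve the primary aim.* The pilot center takes part here, so for its patients the test is temporal. The pair is post-operative and cannot validate the pre-operative algorithm.
- *That a complete pilot rule is ready to apply.* The documents show no equation, cut-off or day. The day 1 calprotectin effect was chosen for the sample size as the least significant finding, so day 1 should not be taken as the pair's day.

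It is also fair to say that refitting the named pair, rather than freezing it, costs only about 0.01 in AUC. The main gain comes from naming it.

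**Conclusion.** The point holds for the post-operative aim. The plan has a named candidate pair from earlier patients, measures it again, and provides only a search in which it competes. With 51 leaks, a searched pair would overstate its AUC by about 0.04 to 0.07, or about 0.03 where one pair clearly dominates. A pair named in advance overstates by about 0.01 if refitted and by essentially nothing with fixed weights, with a 95% half-width of about 0.06 to 0.08 for AUCs of 0.90 to 0.70.

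The optimism figures rest on assumed effects, correlations, candidate numbers and a pair search that the plan does not spell out. The direction does not depend on those choices, but the size does. This is an inexpensive improvement to an analysis choice. It does not invalidate the study or its sample size.

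**What to change.** Add one paragraph to Statistical Analyses:

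1. Before any model search, name CRP plus calprotectin on the pilot's day as the pre-specified post-operative combination.
2. Score it with the pilot's coefficients and cut-off if these are available. Otherwise fit that pair and day without selection, and say so.
3. Report its AUC with a 95% confidence interval, and sensitivity and specificity if a pilot cut-off exists. Show the pilot center and the other two centers separately where numbers allow. Equal shares would give only 51 / 3 = 17 leaks per center, so these splits are descriptive.
4. Report newly searched combinations afterwards as development results, with their gain over this pair.

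The cost is the wording, retrieval of the pilot's details, and a check that the assays are comparable with the pilot's. No extra patients or samples are needed. The downside is that the headline accuracy may be less favourable.
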